### Data collection and management

Data will be collected at four main times: enrolment, during the hospital admission, at hospital discharge and at the 56-day follow-up visit (Table 1). Specially designed case report forms are completed by study staff at each time point, and scanned, verified and committed to a local site database within 48 h of completion using the optical-character-recognition software TeleForm (Hewlett Packard Software, CA, USA). All data in critical fields are verified upon scanning. Completed forms are stored as the source documentation in a locked cabinet, with access restricted to specified study team members. Locator information is stored separately to other case report forms which are identified by unique participant ID number and do not contain any patient identifiable information. Queries based on data in the database are generated weekly, including date, range and logic checks, and sent to sites for resolution.

**Table 1 Tab1:** Schedule of STAMP study activities

	Time-point:	Enrolment	Baseline assessment	TB testing	In-patient stay	Hospital exit	Outpatient Review
	Time On-Study:	Day 0	Day 0	Day 0–1	Day 0+	Day 0+	Day 56
Enrolment:							
Eligibility Screen		X					
Informed consent		X					
HIV confirmation		X					
Study arm allocation		X					
Interventions:							
Collect admission specimens (blood, sputum and urine)			X				
TB screening & issuing results				X			
Assessments:							
Baseline demographic and clinical information			X				
EQ5D			X				X
TB investigations, diagnosis and/or treatment					X	X	X
Vital status					X	X	X
HIV care/ART					X	X	X
Health service use					X	X	X

EQ5D quality of life questionnaire [38]

*ART* antiretroviral therapy

Follow-up at 56-days is undertaken through outpatient appointment attendance at the study site. If participants are unable to attend the outpatient appointment, they are traced by telephone and/or home visit if they have provided prior consent for this to occur. Participants are defined as lost to follow-up if they are unable to be contacted after three tracing attempts after 56-days from enrolment. Quality assurance processes are in place to check all consent forms, screening case report forms, laboratory case report forms and a random sub-sample of all other case report forms.

### Statistical analysis

The trial profile will be summarised using a CONSORT flow chart, including reasons for non-eligibility and non-enrolment (Fig. 2) [32]. All analyses will be conducted by initially assigned study arm in an intention-to-treat analysis, and adjusted for randomisation site. Baseline variables will be presented by study arm.

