### Study procedures

After obtaining written informed consent from eligible patients, a study nurse will collect data at baseline to determine clinical history, including TB symptoms, past history of TB and HIV care, vital signs and nutritional and performance status. Venepuncture for haemoglobin concentration and CD4 cell count will be conducted and single sputum sample and up to 50mls of urine will be collected from all participants, irrespective of study arm. If sputum and/or urine samples cannot be spontaneously produced, participants will remain in the study but no further samples for TB investigation will be arranged by the study team. However, the responsible medical team will remain at liberty to arrange further TB investigations that are available as standard of care at the study hospital.

A randomisation list stratified by study site using computer generated random block size will be generated. Randomisation will occur at enrolment, but the study team will be masked to study arm allocation. When TB samples (sputum and/or urine) from participants arrive in the laboratory, the study laboratory technician will identify the allocated study arm by opening a sealed envelope marked with the unique participant ID, and determine which samples will be screened for TB. Urine from participants randomised to the standard of care arm will not be tested for TB and will be safely discarded. TB-LAM assays will be read by the laboratory technician and results will be deemed as positive using the grade 1 cut-off on the manufacturer’s reference card. 20 % of TB-LAM assays will read by a second, blinded reader for quality control.

TB screening tests will only be processed during office working hours on weekdays. Once the TB screening tests have been completed (anticipated to be within 24-48 h of sample collection), the results will be issued whilst maintaining masking of the study arm and responsible medical teams (reported as either ‘TB screening test positive’, ‘TB screening test negative’ or ‘TB screening test not done’). Rifampicin resistance results, when available, will also be communicated to the medical teams.

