**Fig. 2 Fig2:**
[figure not shown]
CONSORT flow diagram

For the primary outcome the risk difference and odds ratio, and their associated 95 % confidence intervals for the effect of study arm on mortality risk will be calculated. The primary analysis of this endpoint will assume participants who are lost to follow-up before 56 days have not died. Sensitivity analyses will be conducted to assess assumptions made regarding missing data and patients lost to follow-up. A sub-group analysis of the primary outcome will be conducted for the following variables: study site, calendar time, baseline CD4 cell count (<100 or >100 cells/μL), presence of severe anaemia (Hb <80 g/L) and clinically suspected TB at admission. The interaction effects by subgroup will be investigated and p-values reported.

Secondary outcomes (as defined above) will be compared between study arms using logistic regression for binary outcome and survival analysis with Kaplan-Meier curves and Cox proportional hazards for time to event. All analyses will be adjusted for randomisation site.

A statistical analysis plan documents the analysis of all trial outcomes in detail, and was reviewed by the Data Safety and Monitoring Board (DSMB).

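### The article names site as the only covariate for all analyses, forgoing a modest gain in precision from CD4, haemoglobin and performance status already measured at Day 0

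*Protocol article*

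**What the plan says.** The Statistical analysis section sets the adjustment for every analysis: "All analyses will be conducted by initially assigned study arm in an intention-to-treat analysis, and adjusted for randomisation site". After the secondary outcomes it repeats the point: "All analyses will be adjusted for randomisation site". Site is also the stratification factor (Study procedures): "A randomisation list stratified by study site using computer generated random block size will be generated".

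The same Study procedures section lists what is measured at baseline in all participants. This includes "vital signs and nutritional and performance status", and also: "Venepuncture for haemoglobin concentration and CD4 cell count will be conducted". Table 1 places the baseline assessment and specimen collection at Day 0.

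In the analysis text these variables appear only as subgroup factors: CD4 cut at 100 cells/μL, and "presence of severe anaemia (Hb <80 g/L) and clinically suspected TB at admission". The effect measures for 56-day mortality are "the risk difference and odds ratio, and their associated 95 % confidence intervals". Participants lost before day 56 are counted as not having died.

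**The concern.** When baseline variables predict the outcome, a pre-specified adjustment narrows the interval for the treatment effect without recruiting anyone. Here the candidates are taken at Day 0, under masking and before screening results are issued, so adjusting for them is safe.

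The precision matters most for the smaller of the two design effects, a 20% relative reduction from 25% mortality. The Sample size justification claims 80% power for it, with almost nothing to spare at the upper end of the stated loss. The other two power statements have ample room.

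A related point is the scale of reporting. The design target is a relative reduction in risk, but the only relative measure named is the odds ratio. At 25% control mortality a risk ratio of 0.80 corresponds to an odds ratio of (0.20/0.80)/(0.25/0.75) = 0.75. An odds ratio of 0.80 corresponds to a risk ratio of 0.842, which is a 16% reduction.

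**Working it through.** **Inputs from the article.** 1300 per arm, 1:1; control mortality 25%; 20% relative reduction, so 25% versus 20%; two-sided 5%; 10–15% loss; lost participants counted as alive.

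**Input not in the article.** R², the share of variance in 56-day death explained by the baseline covariates. I take 0.02 to 0.20 as an assumed range. In a logistic-normal simulation at an average risk of 22.5%, C-statistics of about 0.64, 0.72 and 0.79 gave R² of about 0.04, 0.12 and 0.21.

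**Formula.** Two-proportion test with pooled null variance, no continuity correction:

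power = Φ[(d − 1.96·SE₀)/SE₁], where d = p₁ − p₂, SE₀ = √(2p̄(1−p̄)/n) and SE₁ = √((p₁(1−p₁)+p₂(1−p₂))/n).

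**Step 1: the plan's own figure.** Dropping 15% of participants leaves 1300 × 0.85 = 1105 per arm. Then d = 0.05, SE₀ = 0.01777, SE₁ = 0.01773, and power = Φ(0.856) = 80.4%. At 10% loss (1170 per arm) it is 82.6%. The stated 80% reproduces. Conversely, 80% power needs 1094 per arm, and 1094/0.85 rounds up to 1288, against 1300 planned.

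**Step 2: the planned handling of loss.** The primary analysis keeps all 1300 and counts the lost as alive. If loss is equal between arms and independent of death, each risk is multiplied by (1 − loss).

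- 10% loss: 22.5% versus 18.0%, d = 0.045, SE₀ = 0.01576, SE₁ = 0.01574, power = Φ(0.896) = 81.5%.
- 15% loss: 21.25% versus 17.0%, d = 0.0425, SE₀ = 0.01543, SE₁ = 0.01540, power = Φ(0.796) = 78.7%.

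**Step 3: effect of adjustment.** Adjustment multiplies the SE of the marginal risk difference by √(1 − R²), equivalent to an effective n of 1300/(1 − R²).

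| Assumed R² | SE reduction | Effective n per arm | Power, 10% loss | Power, 15% loss |
|---|---|---|---|---|
| 0 (site only) | – | 1300 | 81.5% | 78.7% |
| 0.02 | 1.0% | 1327 | 82.3% | 79.5% |
| 0.05 | 2.5% | 1368 | 83.4% | 80.7% |
| 0.10 | 5.1% | 1444 | 85.3% | 82.8% |
| 0.20 | 10.6% | 1625 | 89.1% | 86.9% |

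The R² that counts is for the outcome as analysed. Recording some deaths as survival weakens the association between covariates and outcome, so R² under this rule will be lower than for true mortality.

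**Step 4: scale.** Under the same loss assumption the risk ratio is unchanged (0.17/0.2125 = 0.80), while the risk difference shrinks from 5.0 to 4.25 points at 15% loss. A risk ratio therefore reads directly against the design target.

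**The case against.** The strongest reply is that nothing here is wrong. Site is what the randomisation is stratified on, the test is valid, and the stated 80% power is met without further covariates when losses are simply dropped. All of that stands.

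The wording also does not say that site is the only covariate. The article refers to a SAP that covers all outcomes in detail, and that SAP may add adjusted analyses. This too stands, and it makes the point conditional. Even so, the article gives the adjustment twice, for all analyses, so the point concerns a stated choice and not an omitted detail.

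A reader might infer that the listed variables are strong predictors of death and that a large gain is being lost. The article gives no figure for their prognostic strength, so only a range can be shown, and its lower end is under one percentage point of power.

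A reader might also infer that no reported measure matches the design target. The article does not support that: its text, "For the primary outcome the risk difference and odds ratio", includes an absolute measure, and 25% versus 20% is a 5-point risk difference. The gap is on the relative scale only.

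Finally, the change is not free. Recruitment began in October 2015 (Discussion), the DSMB has reviewed the SAP, and the study statistician is not masked (Study design). Covariates chosen mid-trial by someone who can see allocation would lack credibility. That objection shapes the fix but does not remove the point.

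**Conclusion.** The point holds as a missed efficiency. The site-adjusted analysis is valid, but the article forgoes precision that data already collected could supply.

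The size is modest and uncertain: a standard error about 1% to 11% smaller over the assumed R² range. Under the planned rule for loss, power for 25% versus 20% is 81.5% at 10% loss and 78.7% at 15% loss. At 15% loss, an R² of 0.05 is enough to bring it back above 80%, to about 80.7%, and 0.10 gives about 82.8%; an R² of 0.02 is not enough.

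These figures rest on loss being equal between arms and independent of death, on the pooled two-proportion test, and on R² values that the article does not provide.

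**What to change.** If the SAP already specifies an adjusted primary analysis, align the article with it. Otherwise, before any comparative data are seen, amend the plan as follows.

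- Someone masked to allocation fixes a short covariate list from variables already collected: site, CD4 and haemoglobin as continuous terms, and performance status.
- State a simple rule for missing baseline values.
- Report the standardised (marginal) 56-day risk difference with its 95% CI as the primary result, and the risk ratio from the same model because the design target is relative. If an odds ratio is also given, say whether it is conditional or marginal: a covariate-conditional odds ratio is a different quantity from the site-adjusted one (non-collapsibility).
- Keep the site-only estimate as a sensitivity analysis.

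No new data or participants are needed. The cost is slightly more programming, one added assumption for missing covariates, and a documented amendment during recruitment.

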**Fig. 2 Fig2:**
[figure not shown]
CONSORT flow diagram

For the primary outcome the risk difference and odds ratio, and their associated 95 % confidence intervals for the effect of study arm on mortality risk will be calculated. The primary analysis of this endpoint will assume participants who are lost to follow-up before 56 days have not died. Sensitivity analyses will be conducted to assess assumptions made regarding missing data and patients lost to follow-up. A sub-group analysis of the primary outcome will be conducted for the following variables: study site, calendar time, baseline CD4 cell count (<100 or >100 cells/μL), presence of severe anaemia (Hb <80 g/L) and clinically suspected TB at admission. The interaction effects by subgroup will be investigated and p-values reported.

Secondary outcomes (as defined above) will be compared between study arms using logistic regression for binary outcome and survival analysis with Kaplan-Meier curves and Cox proportional hazards for time to event. All analyses will be adjusted for randomisation site.

A statistical analysis plan documents the analysis of all trial outcomes in detail, and was reviewed by the Data Safety and Monitoring Board (DSMB).

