### Outcomes

The primary outcome is risk of all-cause mortality at 56-days following enrolment. Secondary outcomes are: time to all-cause mortality; proportions of patients with (i) microbiologically confirmed and (ii) clinically diagnosed TB disease; time to TB diagnosis and commencement of TB treatment; proportions of patients receiving antimicrobials and ART; and (i) duration of hospital admission, (ii) cumulative incidence of hospital readmission, and (iii) cumulative incidence of loss to follow-up. Outcomes will be ascertained by patient interview and review of medical notes during in-patient admission, and patient interview for vital status at 56-days post enrolment. This will be supplemented with information from patients’ next of kin for those lost to follow-up.

Microbiologically confirmed TB is defined as at least one positive smear-microscopy, Xpert, or culture positive result on any specimen or a positive urine TB-LAM result. Clinically diagnosed TB is defined as having a compatible clinical illness or radiological disease and/or the decision of the responsible clinical team to commence TB treatment in the absence of any positive microbiological tests for TB.

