### Sample size justification

Sample size calculations were based upon unpublished data from the trial sites, which showed a mortality of HIV-positive medical in-patients of 21–23 % during hospital admission and are supported by subsequently published meta-analyses on hospitalised HIV-positive patients in Africa [2, 30]. We assumed that 56-day mortality would be 25–30 % in the standard of care arm and, based upon post-mortem prevalence of TB, we estimated 40–50 % of deaths in the standard of care arm would be TB-related.

The sensitivity of the intervention for diagnosing TB disease was assumed to be 80 % (a 3-fold increase in diagnostic yield compared to sputum alone) based upon a background study [14]. An observational study of early-initiation of TB treatment among HIV-positive smear-negative hospital in-patients observed a reduction in mortality at 2-months of 47 % in patients whose TB treatment was expedited by use of WHO-recommended diagnostic algorithm compared to standard practice [31]. Our study was powered to detect a 40–50 % reduction in TB-related mortality, and assuming half of deaths are TB related, this would equate to a 20–25 % reduction in all-cause mortality. Our sample size of 1300 patients per arm would provide 90 % power to detect a 25 % reduction in mortality and 80 % power to detect a 20 % reduction in mortality, assuming an all-cause mortality of 25 % in the ‘standard of care’ arm and a 2-sided type 1 error of 5 % and 10–15 % loss to follow-up. If the 56-day mortality was unexpectedly lower (20 %) in the standard of care arm, our sample size would still provide 80 % power to detect a 25 % reduction in all-cause mortality.

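### Kaplan-Meier is named for time to TB diagnosis and TB treatment, which death can preclude; with deaths censored it modestly overstates their cumulative incidence

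*Protocol article*

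**What the plan says.** The Statistical analysis section of the protocol article assigns methods by outcome type. "Secondary outcomes (as defined above) will be compared between study arms using logistic regression for binary outcome" covers one group; the rest get "survival analysis with Kaplan-Meier curves and Cox proportional hazards for time to event".

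The Outcomes section opens its secondary list with "Secondary outcomes are: time to all-cause mortality" and then includes "time to TB diagnosis and commencement of TB treatment". These are plainly time-to-event outcomes. The list also has "i) duration of hospital admission, (ii) cumulative incidence of hospital readmission, and (iii) cumulative incidence of loss to follow-up". The article does not say which method applies to these three.

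The Sample size justification gives the mortality background. Site data showed "mortality of HIV-positive medical in-patients of 21–23 % during hospital admission", and 56-day mortality in the standard-of-care arm is assumed to be 25–30%, with 20% as a low scenario.

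Competing events are not mentioned, nor is how a death enters a non-fatal time-to-event analysis. Detail is referred to a statistical analysis plan that is not shown.

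**The concern.** One method is named for two different kinds of outcome. Nothing competes with all-cause death, so Kaplan-Meier estimates its risk directly. TB diagnosis and TB treatment are different, because death removes the patient from any chance of the event. Censoring at death treats that patient as still able to be diagnosed or treated later. The complement of the curve then estimates incidence as if nobody died, not the proportion of admitted patients who were diagnosed or treated.

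This matters because time to TB treatment is the step by which the screening strategy is meant to save lives, and the Background stresses that many patients die with TB undiagnosed. The same issue would reach readmission and length of stay if they are analysed as time to event. For length of stay there is an opposite hazard: if death is counted as the end of the admission, the arm with more early deaths appears to have shorter stays.

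**Working it through.** The plan gives no figure for these outcomes, so there is none to reproduce. Its mortality figures are the only inputs from the documents. **All event rates and hazard shapes below are assumptions.**

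**1. Constant hazards over 56 days.** Let E be the true proportion with the event by day 56 and D the proportion dying first.

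- Total cumulative hazard: Λ = −ln(1 − E − D)
- Event part: Λe = Λ × E/(E + D)
- Kaplan-Meier complement, deaths censored: 1 − exp(−Λe)

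Example, E = 20% and D = 25%: Λ = −ln(0.55) = 0.598; Λe = 0.598 × 0.20/0.45 = 0.266; 1 − exp(−0.266) = 23.3%.

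| True E | Reads as, D = 20% | Reads as, D = 25% |
|---|---|---|
| 10% | 11.2% | 11.6% |
| 20% | 22.5% | 23.3% |
| 30% | 34.0% | 35.3% |

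For a readmission-type event the excess is about 1–5 points.

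**2. TB treatment, mostly started early.** Take a constant death hazard giving 25% by day 56. Set the treatment hazard high in days 0–5 and at one-twentieth of that afterwards. A true 15%, 20% and 30% then read as 15.9%, 21.1% and 31.6%, an excess of about 1–2 points. About 19–22% die untreated.

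**3. Front-loaded deaths.** Use daily steps t = 0 to 55. The death hazard is 0.0201·exp(−t/14), scaled to 25% by day 56. With event hazard e(t) and death hazard d(t), true incidence is Σ S(t)·e(t), where S(t) is the product of (1 − e − d) over earlier days. The Kaplan-Meier complement is 1 − Π(1 − e).

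| Outcome and assumed hazard | True | Kaplan-Meier | Excess (points) |
|---|---|---|---|
| TB treatment, 0.05·exp(−t/7) | 29.1% | 31.7% | about 2.5 |
| Readmission, 0.003/day from day 10 | 10.1% | 12.9% | 2.8 |
| Readmission, 0.005/day | 16.1% | 20.6% | 4.5 |
| Readmission, 0.008/day | 24.2% | 30.9% | 6.7 |

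**4. Discharge alive, if a curve were drawn.** Let D be in-hospital deaths and R the proportion still admitted at day 56, with E = 1 − D − R. The complement is 1 − R^(E/(E + D)).

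- D = 22%, R = 1%: true 77% reads as 97.2% (20.2 points).
- D = 22%, R = 5%: true 73% reads as 90.0% (17.0 points).
- Discharge hazard 0.08/day and death hazard 0.0226/day (about 22% in-hospital deaths): true 77.8% reads as 99.1% (21.3 points).

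Across D = 21–23% and R = 1–5% the excess runs from 16.3 to 21.1 points.

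**5. Arm differences under the step 3 and 4 hazards, mortality 25% against 20%.**

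- TB treatment, with hazard coefficient 0.05 against an assumed 0.065: the true difference is 36.7 − 29.1 = 7.6 points; Kaplan-Meier gives 39.2 − 31.7 = 7.5.
- Readmission with equal hazards: the true differences are 0.6, 0.9 and 1.4 points; Kaplan-Meier gives 0.
- Discharge alive with equal discharge hazards and the in-hospital death hazard 25% lower: 82.2% against 77.8%; Kaplan-Meier gives 99.1% in both arms.

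**6. Readmission counted from discharge.** The planning figures leave 25 − 23 = 2 to 30 − 21 = 9 points of post-discharge deaths. Over 46 days with constant hazards among those discharged, and the step 3 readmission hazards, the relative excess is only about 1–6%.

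**The case against.** The strongest reply is that the article states no error. It gives one sentence matching outcome types to method families, never says deaths are censored, and points to a statistical analysis plan for the detail. That makes the bias conditional. It does not remove the point, because the article names a method, and the usual form of that method censors deaths.

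Several stronger readings are tempting and not supported:

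- **That readmission and discharge are assigned to Kaplan-Meier.** They are not. Readmission by day 56 could be a binary outcome under logistic regression, with no such bias, and time to discharge is not a listed outcome. Starting readmission at discharge would also shrink the excess (step 6). The largest figures are therefore conditional.
- **That the Cox results are biased.** Cox regression with deaths censored validly estimates a cause-specific hazard ratio. It is simply not a comparison of cumulative incidence.
- **That a quarter of patients die before the event.** The 25% is the assumed control-arm mortality by day 56. Deaths after TB treatment or readmission do not compete; in the step 3 illustration about 20% die before TB treatment.
- **That the arm comparison for TB treatment is seriously distorted.** In step 5 it moves by about 0.1 point. The proportions with confirmed and clinically diagnosed TB are also separate binary outcomes.
- **That the curves feed the cost model.** The Economic analysis section bases costs on participants' resource use and does not mention these curves.

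**Conclusion.** The point holds as a minor one. For time to TB diagnosis and TB treatment, Kaplan-Meier with deaths censored overstates cumulative incidence. The direction is certain whenever deaths precede the event. The size, calculated for TB treatment, is about 1–3 points if treatment starts early and 25% die by day 56. If readmission or discharge alive were analysed the same way, the excess would be about 1–7 points (less if counted from discharge) and about 17–21 points respectively; a genuine arm difference produced by fewer deaths could then disappear from the curves. These sizes rest on assumed event rates and hazard shapes, because the article gives none, and on deaths being censored, which it does not state. The primary outcome and time to all-cause death are not touched.

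**What to change.** - Keep Kaplan-Meier and Cox for all-cause death.
- For time to TB diagnosis and time to TB treatment, report Aalen-Johansen cumulative incidence with death as the competing event, and the 56-day difference between arms with its confidence interval. Do the same for readmission and length of stay if they are analysed as time to event.
- Label the Cox result for these outcomes a cause-specific hazard ratio.
- Do not count death as discharge in length of stay; report discharge alive and death in hospital separately.

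The cost is a little wording and some additional analysis in standard software. Table 1 shows vital status, TB investigations and treatment, and health service use already collected during the stay, at hospital exit and at day 56. Sample size and primary analysis do not change.
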